### Randomization and Allocation

We will use a block- randomization, stratified in groups for center to assign participants to the high- intensity exercise group, moderate- intensity exercise group and the control group in a 1:1:1 ratio. For the hierarchical random assignment operation, the statistical unit responsible adopted the SAS version 9.2 statistical software (procedure 'PROC PLAN') to complete program writing and randomization operations. The random distribution results will be released through the network of a central random distribution system. The results of random allocation will be managed by a person designated by the research group, and the results will be executed independently by clinicians. Due to the interventional study design, blinding is impossible for patients and clinical operators. However, the examiners, researchers collecting data on outcome indicators, data managers, and statisticians will be blinded.

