### Outcome Measures

The primary outcome for the HF-EI trial is the change in peak VO_2_ and Minnesota Living with Heart Failure Questionnaire scores (MLHFQ)after 12 weeks. We choose the common primary outcomes in order to obtain the comprehensive effect of different exercise intensities on HFrEF treatment. Aerobic exercise has a well-known positive effect on patients with HFrEF in exercise capacity and quality of life, and peakVO_2_ is an important indicator for evaluating the prognosis of HF (22, 40).

Secondary outcomes included, AT oxygen uptake, 6MWD, LVEF, NT pro-BNP, PHQ-9, GAD-7, all-cause- mortality, hospitalization events for HF, major cardiovascular events, and adverse events.

The test indicators require patients to be measured at the hospital rehabilitation center. The test details are as follows:

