#### Baseline Data

We will monitor the demographic data, medical history, physical status, laboratory tests (NT pro-BNP), cardiology diagnostic tests (LVEF), cardiopulmonary exercise tests (peak VO_2_, AT oxygen uptake), 6MWD, scale score(MLHFQ, PHQ-9, and GAD-7)and medications during the baseline period. Baseline data will be collected through outpatient consultation and medical record review.

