### Statistical Methods

The calculation of the sample size will be based on the primary outcome of the RCT. The sample size calculation was performed using PASS V11.0 (NCSS Company of the United States) with the following calculation formula:

$$\begin{array}{l} n=\Psi^{2}\left[\sum_{i=1}^{k}s_{i}^{2}/k\right]/\left[\sum_{i=1}^{k}{\left({\bar{X}}_{i}-\bar{X}\right)}^{2}/\left(k-1\right)\right]\left(k\;=\;3\right) \end{array}$$

The parameters are set to double-sided α = 0.05, β = 0.1, Power = 1–β = 90%, the average difference in peak VO_2_ of the three groups were 0, 2, 4(ml/kg/min) and the average difference in MLHFQ of the three groups were 2, 12, 10. The corresponding standard difference values of peakVO_2_ were 6, 4, 6 (ml/kg/min) and MLHFQ were 5, 18, 16.

The parameter estimation is based on the results of previous researches (22, 42, 43).

A total of 180 cases were required for the three groups, 60 patients in each group, considering the 20% loss to follow-up rate and stratification factors. Because each of the primary endpoints can be individually reflected in clinical significance. Therefore, if one of the two primary endpoints of the intervention group improves significantly, the study is successful.

Blinded statistical analysis will be performed by qualified statisticians using PASW Statistics 18.0 (IBM SPSS Inc., Armonk, New York, USA). The measurement data will be expressed as mean ± standard deviation (x ± s), measurement data by *t* test, and count data by chi-square test. The clinical events of the treatment groups will be statistically compared, according to the principle of intention-to-treat. The Kaplan–Meier method will be used to calculate the cumulative event rate. The event time of all patients will be measured starting from the randomization time (time zero). We will collect all available information on clinical events until the last patient contact, including patients who withdraw consent or those lost to follow-up. Relative risk (RR) will be calculated using the Cox proportional hazard model. If a sufficient number of events occur, the Kaplan–Meier curve will be used for stratified analysis of the exercise group, and the log-rank test will be used to test the difference in survival. The significance level will be set at *p* < 0.05.

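### The 12-week changes in peak VO2 and MLHFQ are compared by unadjusted t tests, without baseline as a covariate or centre as a factor: a valid analysis, but less precise than the collected data allow

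*Protocol article*

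**What the plan says.** The Statistical Methods section assigns "measurement data by *t* test, and count data by chi-square test". No covariate and no centre term is attached to that sentence. The only other regression mentioned for outcomes, apart from the survival models for clinical events, is an exploratory dose-effect analysis in the Introduction.

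Three other sections bear on the choice:

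- Outcome Measures defines the primary outcome as "the change in peak VO_2_ and Minnesota Living with Heart Failure Questionnaire scores (MLHFQ)after 12 weeks".
- Baseline Data lists "cardiopulmonary exercise tests (peak VO_2_, AT oxygen uptake), 6MWD" and "scale score(MLHFQ, PHQ-9, and GAD-7)and medications during the baseline period", so the baseline value of each primary outcome will be on file.
- Randomization and Allocation states "We will use a block- randomization, stratified in groups for center". Setting and Participants names three sites.

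The sample size paragraph in Statistical Methods says that stratification factors were taken into account in reaching 180 patients. The analysis sentence in the same section does not use them.

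**The concern.** A change score uses the baseline by subtracting all of it, which amounts to fixing the regression slope of the week-12 value on baseline at 1. When the correlation between the two is below 1 and their variances are equal, the best slope is smaller than 1. Fixing it at 1 then leaves avoidable noise in the comparison. Centre enters the design through stratification but not the analysis, so any difference between centres stays in the error term.

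What is at stake is precision in the comparisons the trial cares about most. The Introduction says the main comparisons are moderate against high intensity and moderate intensity against daily activities. These are pairwise, and some of the planned differences are small relative to the planning SDs. Adjustment would narrow the confidence intervals and would also account for chance baseline imbalance with 60 patients per arm.

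**Working it through.** **Inputs from the article (Statistical Methods).** Two-sided alpha 0.05 and power 90%; peak VO2 differences 0, 2, 4 with SDs 6, 4, 6 ml/kg/min; MLHFQ differences 2, 12, 10 with SDs 5, 18, 16; 20% loss; 60 per group, 180 in total. Evaluable per arm: 60 × 0.8 = 48. The article does not label which value belongs to which arm.

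**Inputs assumed.** The SDs are SDs of the 12-week change; baseline and week-12 variances are equal; r runs from 0.5 to 0.9; centre explains 1% to 10% of the variance. The article gives neither r nor the centre share.

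**Step 1: the stated sample size.** The article's formula is that of a three-group F test. For peak VO2 the mean variance is (36 + 16 + 36)/3 = 29.33 and the sum of squared deviations of the means is 4 + 0 + 4 = 8. With 48 per group the noncentrality is 48 × 8 / 29.33 = 13.09, which gives 90.4% power. Then 48/0.8 = 60 per group, 180 in total. For MLHFQ, 47 per group are needed, 59 after loss, and power at 48 is 90.9%. The stated size therefore reproduces, with no adjustment for baseline or centre.

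**Step 2: variance of a change score against baseline adjustment.** With common SD s at both times:

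- change score: 2s²(1 − r)
- baseline-adjusted: s²(1 − r²)
- ratio: (1 − r²) / [2(1 − r)] = (1 + r)/2

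**Step 3: power for a 2 ml/kg/min difference, SDs 4 and 6, 48 per arm (Welch).** Unadjusted standard error: √(16/48 + 36/48) = 1.041, power 47.6%. With adjustment the standard error is multiplied by √[(1 + r)/2]:

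| Assumed r | Variance factor | Standard error | Power |
|---|---|---|---|
| none (t test on change) | 1.00 | 1.041 | 47.6% |
| 0.5 | 0.75 | 0.901 | 59.2% |
| 0.6 | 0.80 | 0.931 | 56.5% |
| 0.7 | 0.85 | 0.960 | 54.0% |
| 0.8 | 0.90 | 0.987 | 51.7% |
| 0.9 | 0.95 | 1.014 | 49.5% |

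At r = 0.6, 48 evaluable patients carry the information of 48/0.80 = 60. An equal-variance calculation for the same contrast gives 48.5% unadjusted, 60.2% at r = 0.5 and 52.6% at r = 0.8.

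**Step 4: centre.** If centre explains a share c of the variance and allocation is balanced within centre, adjustment multiplies the variance by 1 − c, that is 0.99 to 0.90 for c of 1% to 10%. An unadjusted test then has actual two-sided alpha 2[1 − Φ(1.96/√(1 − c))]: about 0.049 at c = 1% and 0.039 at c = 10%. The error is on the conservative side.

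**Step 5: a check on the replacement model.** If all three arms are fitted with one common residual variance, the pooled MLHFQ SD is √[(25 + 324 + 256)/3] = 14.2. For the two arms with SDs 18 and 16 the relevant SD is √[(324 + 256)/2] = 17.0. Using 14.2 there would turn a nominal 5% test into one of about 10%, since 2[1 − Φ(1.96 × 14.2/17.0)] = 0.10. The safeguard in the fix is there for this reason.

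**The case against.** Several points can be made for the plan as written, and most of them stand.

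- A reader might infer that baseline is ignored. It is not: both primaries are changes, so baseline enters by subtraction. The right comparison is a change score against baseline adjustment, factor (1 + r)/2, and the gain shrinks as r approaches 1.
- A reader might infer that the t test gives biased estimates or too many false positives. It does neither. A comparison of changes is unbiased under randomization, and leaving out centre is conservative.
- A reader might take the 10% type I error in Step 5 as a fault of the plan. A two-sample t test uses only the two arms compared, so that risk belongs to a three-arm model with a common variance and not to the stated test.
- Low pairwise power might be blamed on the missing adjustment. It comes mainly from sizing on a three-group F test and then comparing pairs, which is a separate matter. Even at r = 0.5 adjustment reaches only 59%.
- The article condenses a fuller protocol, and covariates are often left to the statistical analysis plan. That would answer a complaint about silence. Here the article names the test, so the point concerns a stated choice. If the analysis plan already specifies an adjusted model, the two documents need only be aligned.

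**Conclusion.** The point holds as one of efficiency. The stated analysis is valid but discards precision that the collected baseline values and the stratified design make available without extra patients. The gain is real but modest: a 5% to 25% cut in variance from baseline for r of 0.9 down to 0.5, and a further 1% to 10% from centre if it explains that share. For the 2 ml/kg/min contrast this means about 2 to 12 percentage points of power above 48%. These figures rest on equal baseline and week-12 variances, on the planning SDs being SDs of change, and on values of r and of the centre share that the article does not give. The finding does not invalidate the sample size calculation and does not show bias. It is a change worth making while analysts are still blinded, not a condition for the trial's validity.

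**What to change.** Replace the t test for both primary outcomes and the continuous secondary outcomes by a linear model of the week-12 value (or the change) on arm, baseline value and centre. Report adjusted pairwise differences with 95% confidence intervals. If all three arms are fitted in one model, allow arm-specific residual variances or use robust standard errors, because the planning MLHFQ SDs (5, 18, 16) differ widely.

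The cost is a change of wording in the analysis section and the statistical analysis plan, with no new data, visits or patients. The Trial Organization section says recruitment is under way and the statisticians are to be blinded, so the change should be dated and recorded before anyone sees outcomes by arm.

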3. LVEF <0.4
4. NYHA I-III.
5. Clinical symptoms are stable for at least 2 weeks
6. The dose of angiotensin-converting enzyme inhibitor/angiotensin receptor antagonist/angiotensin receptor enkephinase inhibitor, beta-blocker, aldosterone inhibitor and other drugs was stabilized for at least 2 weeks.
7. Written informed consent.

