#### Outcome Assessments

Physical examination, exercise steps, medication use, and clinical events (all-cause-mortality, hospitalization events for HF, major cardiovascular events, and adverse events) will receive outpatient follow-up in the 4th and 8th weeks after random assignment. At 12 weeks after randomization, physical examination, laboratory tests, cardiology diagnostic tests, cardiopulmonary exercise test, 6MWD, scale scores, exercise steps, medication, and clinical events will receive outpatient follow-up visits. 4–12 months after randomization, clinical events will be followed up by telephone every month. Both the baseline survey and follow-up will be conducted by two physicians.

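### Kaplan-Meier is the only method named for cumulative event rates; for HF hospitalization, where deaths would ordinarily be censored, it modestly overstates the absolute rate

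*Protocol article*

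**What the plan says.** The Outcome Measures section of the protocol article includes these among the secondary outcomes: "all-cause- mortality, hospitalization events for HF, major cardiovascular events, and adverse events". The Outcome Assessments section puts the same four under one label: "clinical events (all-cause-mortality, hospitalization events for HF, major cardiovascular events, and adverse events". Mortality and HF hospitalization are thus separate outcomes, and neither section combines them.

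Statistical Methods then covers clinical events as a group:

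- Cumulative rates: "The Kaplan–Meier method will be used to calculate the cumulative event rate".
- Time origin: "The event time of all patients will be measured starting from the randomization time (time zero").
- Comparison between arms: "Relative risk (RR) will be calculated using the Cox proportional hazard model", with a log-rank test if events are numerous enough.
- Length of follow-up, from Outcome Assessments: "4–12 months after randomization, clinical events will be followed up by telephone every month".

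The article does not say how a death is handled when the outcome is a non-fatal event. It does not mention competing risks or a cumulative incidence function.

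**The concern.** A patient who dies can no longer be hospitalized for heart failure. Kaplan-Meier has only two ways to close a patient's follow-up: an event or a censoring. When HF hospitalization is analysed alone, counting the death as an event would create a composite that the article does not define. The ordinary course is therefore to censor at death.

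The estimator then assumes that patients who died would have gone on to be hospitalized at the same rate as those still at risk. One minus Kaplan-Meier describes a setting in which nobody dies, not the share of randomized patients who are actually hospitalized within 12 months. It lies above that share as soon as a death precedes later hospitalizations.

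What is at stake is how well the absolute rates describe each arm in a trial that sets out to assess safety as well as efficacy. For similar hospitalization hazards, the overstatement is larger in an arm with more deaths, so absolute differences between arms can shift a little.

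**Working it through.** **The plan's own figure.** There is none to reproduce. The article states no event rate, event count or mortality, and its sample size rests on peak VO2 and MLHFQ only.

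**Inputs.** From the article: Kaplan-Meier for the cumulative rate, randomization as time zero, 12 months of event follow-up, and 60 patients per arm. Assumed: constant hazards over 12 months, one minus Kaplan-Meier for HF hospitalization of h = 15, 25 or 35%, and a 12-month death risk of d = 5, 10 or 15% in patients not yet hospitalized.

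**Formulas.**

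- Hospitalization hazard: λh = −ln(1 − h)
- Death hazard: λd = −ln(1 − d)
- One minus Kaplan-Meier with deaths censored: 1 − exp(−λh) = h
- Cumulative incidence with death competing: CIF = λh / (λh + λd) × [1 − exp(−(λh + λd))]

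**One case in full, h = 25% and d = 10%.** λh = 0.2877 and λd = 0.1054, with sum 0.3930. Then 1 − exp(−0.3930) = 1 − 0.75 × 0.90 = 0.325. CIF = 0.2877 / 0.3930 × 0.325 = 0.238. Kaplan-Meier would report 25.0% against 23.8%, an excess of 1.2 points.

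**The grid.**

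| h (1 − KM) | d | CIF | Excess (points) | Excess as share of h |
|---|---|---|---|---|
| 15% | 5% | 14.6% | 0.4 | 2.5% |
| 15% | 10% | 14.3% | 0.7 | 5.0% |
| 15% | 15% | 13.9% | 1.1 | 7.5% |
| 25% | 5% | 24.4% | 0.6 | 2.4% |
| 25% | 10% | 23.8% | 1.2 | 4.9% |
| 25% | 15% | 23.2% | 1.8 | 7.3% |
| 35% | 5% | 34.2% | 0.8 | 2.3% |
| 35% | 10% | 33.3% | 1.7 | 4.7% |
| 35% | 15% | 32.5% | 2.5 | 7.2% |

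**Lower mortality.** At d = 1% the excess is 0.07 points for h = 15% and 0.16 points for h = 35%. At d = 5% it is at most 0.8 points on this grid, which is 60 × 0.0082 = 0.5 of a patient in an arm of 60.

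**Difference between two arms.** Take h = 25% in both arms, with deaths of 5% in one and 10% in the other. The excesses are 0.6 and 1.2 points, so the difference in Kaplan-Meier rates is off by about 0.6 points. The standard error of a difference between two arms of 60 at 25%, ignoring censoring, is √(2 × 0.25 × 0.75 / 60) = 0.079, or about 8 points.

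**The case against.** The strongest objection is that censoring at death is not written anywhere. The article is silent on it, and censoring rules for secondary events are often left to an analysis plan, which is not shown. The sentence on Kaplan-Meier also does not say which clinical events it covers. All-cause mortality is one of them, and for mortality the method is right. This stands in part: censoring is an inference from how Kaplan-Meier works on a single non-fatal event. But the point is not one of missing detail. The article positively names one estimator for a group of events, only some of which it suits, and an analysis plan that follows that sentence inherits the problem.

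The size is a second objection, and it stands. Patients must be stable ("Clinical symptoms are stable for at least 2 weeks") and in NYHA class I to III, so 12-month mortality may lie at or below the low end of the assumed range. The shift between arms worked out above is small beside the sampling error.

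Four stronger readings are tempting, and the documents do not support them:

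- *The reported rates are certain to be too high.* This needs deaths before hospitalization, censoring of those deaths, and use of Kaplan-Meier for that outcome. With no such death there is no excess.
- *The comparison between arms is invalid.* The Cox model and log-rank test with deaths censored remain valid for cause-specific hazards.
- *The safety conclusion is distorted.* No section bases a safety conclusion on a difference in Kaplan-Meier rates.
- *Adverse-event and major cardiovascular event rates are overstated too.* Adverse events may be handled as counts, for which the article names a chi-square test. Major cardiovascular events are not defined in the article and may already include deaths.

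**Conclusion.** The point holds as a minor one. Following the article as written would ordinarily give an HF hospitalization rate biased upward as an estimate of cumulative incidence. The excess is about 0.4 to 2.5 percentage points under assumed constant hazards, 12-month HF hospitalization of 15 to 35% and death of 5 to 15%. It is under 1 point on that grid when mortality is 5% or less.

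All of these rates are assumptions, because the article gives none. The direction does not depend on them, provided that deaths are censored and that at least one death precedes later hospitalizations. The effect is confined to absolute rates of secondary non-fatal outcomes.

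**What to change.** In Statistical Methods, keep Kaplan-Meier for all-cause mortality and for any composite that includes all deaths. For HF hospitalization and other non-fatal outcomes analysed as time to event, report the Aalen-Johansen cumulative incidence with death as a competing event. If the definition of major cardiovascular events leaves out some deaths, treat those deaths as competing. Keep the Cox model, but label its result a cause-specific hazard ratio rather than a relative risk.

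The cost is one or two sentences in the plan. The estimator may need software beyond the named PASW Statistics 18.0, and the reported rates become slightly lower. Data collection, sample size and the primary analysis do not change.

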### Trial Management and Quality Control

The management structure includes a trial management team, a data monitoring committee, and a trial steering committee.

The trial management team (including two physicians and three investigators) is responsible for the implementation of the trial and will meet weekly to discuss the progress of the trial. The data monitoring committee is composed of three clinicians and two biostatisticians, and independently evaluates the safety, scientific validity and completeness of clinical trials. The data monitoring committee will convene a meeting before the start of patient recruitment and once a month after the patient begins to intervene. The person in charge of the center monitors the intermediate results during the clinical trial. Once serious side effects occur, the trial should be stopped immediately. If there are significant differences in the efficacy of the three groups (HIT group, MIT group, and control group), the trial will be considered to be terminated. Responsibility of the test steering committee is to approve the main research plans and revisions, supervise the test, guide the test, and solve the problems of the test management team. The committee will be composed of four experts and will meet at least once every 6 months.

Before recruitment, the entire research team needs to participate in a training seminar. The data collected in this trial will include questionnaire information, medical chart review and test results. Professionals double-enter the data and store the data confidentially in the electronic database. The person in charge of the sub-center has the right to access the data set of the sub-center, and the person in charge of the project has the right to access the final data set of all the centers. Researchers and sponsors will inform participants and other relevant personnel of the results of the trial by publishing articles. The data quality will be regularly checked by the research assistant and supervised by the supervisor.

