Studies on the effects of exercise-based CR on the mortality and hospitalization rate of patients with HF show conflicting results, possibly attributed to differences in exercise pattern, exercise intensity, patient population selection, compliance, and follow-up time. All factors, especially exercise intensity, may affect the endpoint effect. Therefore, further research is needed to determine optimal exercise intensity to reduce the mortality and HF hospitalization rate.

Since the 1980s, numerous studies have demonstrated the safety and effectiveness of moderate intensity training (MIT) (19, 20). However, recent data suggest that high intensity training (HIT) may offer some advantages over MIT (21–32). Within a specific intensity range, exercise intensity is proportional to the effect. However, higher exercise intensity is associated with higher risk, and a higher need for adjusted to ensure safety and effectiveness in patients with HF. The mainstream sports rehabilitation model in developed countries of Europe and the United States is based on rehabilitation centers and ET under electrocardiogram (ECG) monitoring. A 12-week, three times a week treadmill exercise is used as a classic exercise prescription (33). The advantage is that it considers the efficacy and safety of ET, providing tremendous benefits to patients with HF in the short term. Keteyian et al. found that a moderate amount of exercise (3–7 metabolic equivalent hours per week) in patients with HF reduces the risk of clinical events, and within this range, an increase in the amount of exercise is associated with increased benefits (34). Swank et al. also obtained similar results. After exercise rehabilitation in patients with HF, increased peak oxygen consumption (peak VO_2_) was associated with improved prognosis (35).

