According to the grading standards for exercise intensity proposed by the 2020 European Society of Cardiology (ESC) Guidelines on sports cardiology and exercise in patients with cardiovascular disease, the anaerobic threshold (AT) intensity is moderate, 70% PeakVO_2_ intensity is high intensity (36). We will design a three-arm randomized controlled experiment to explore the effectiveness and safety of moderate exercise intensity (AT intensity) in the treatment of HFrEF. The HIT (70% PeakVO_2_ intensity) group served as the active control group, and the daily activity group served as the placebo control group. Mainly compare MIT and HIT, or MIT and daily activities, and explore the dose-effect relationship of exercise intensity on changes in clinical outcomes through regression analysis. We assume that MIT has a greater impact in the main results than HIT and daily activities.

We will evaluate the efficacy and safety of different aerobic exercise intensities in patients with HFrEF: the HF-EI trial. This study is the first multicenter randomized controlled trial (RCT) on the effects of different aerobic exercise intensities in patients with HFrEF in China. By collecting data on exercise capacity and exercise rehabilitation, we will evaluate the clinical efficacy of exercise-based CR in Chinese patients with HFrEF. Finally, suitable exercise intensity will be recommended for the popularized HFrEF aerobic exercise program for Chinese patients with HFrEF.

The primary objective of the HF-EI trial is to investigate the effects of different exercise intensities on exercise capacity and quality of life in patients with HFrEF. As secondary objectives, the HF-EI trial will evaluate AT oxygen uptake, 6-min walk distance (6MWD), left ventricle ejection fraction (LVEF), N-terminal prohormone of brain natriuretic peptide (NT pro-BNP), the Patient Health Questionnaire-9 (PHQ-9), General Anxiety Disorder-7(GAD-7), all-cause mortality, HF hospitalization, major cardiovascular events, and adverse events.

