### Intervention Group

Patients randomized to receive HIT or MIT training receive 36 supervised training sessions, thrice weekly, in addition to usual care for 12 consecutive weeks of aerobic ET. Patients will be regularly encouraged to exercise on other days. The duration of each exercise session in the high intensity training group is 30 min, and the duration of each exercise session in the moderate intensity training group is 35–42 min. It is estimated that the high intensity training group and the moderate intensity training group have similar energy expenditure (38, 39). Table 2 summarizes the training program for the HF-EI trial. Participants who have serious adverse clinical events during the intervention will immediately stop the intervention measures and withdraw from this clinical study.

**Table 2 T2:** Training program.

**Group**	**Intervention**			
	**Frequency**	**Duration**	**Intensity**	**Form**
High intensity training group	3 times per week	30 min	70% peak VO_2_	Centre-based rehabilitation: treadmill. Home-based cardiac rehabilitation: walk.
Moderate intensity training group	3 times per week	35–42 min	AT	Centre-based rehabilitation: treadmill. Home-based cardiac rehabilitation: walk.
Control group	Daily activities.

*peak VO_2_, peak oxygen consumption; AT, anaerobic threshold*.

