AT relates to the point when the exercise load increases to a certain amount and the tissue demand for oxygen exceeds the amount that the circulation can provide, and the tissues undergo anaerobic metabolism to provide more energy. The critical point from aerobic metabolism to anaerobic metabolism is called AT, expressed as the threshold oxygen consumption of anaerobic metabolism (VO_2_ AT), equivalent to 50–60% of peak oxygen consumption, and directly detected by CPET (44). The advantages of using AT as the basis for formulating exercise prescriptions are sub-maximal exercise intensity, which can prevent the continuous increase of lactic acid levels, avoid hyperventilation and shortness of breath, avoid metabolic alkalosis, reduce the occurrence of overload on the heart and arrhythmia, and ensure high safety. Aerobic exercise with the intensity of the AT has protective effects on CHF, confirmed by the literature (45). For patients with HFrEF, exercise intensity is a range, not a point; AT belongs to sub-maximum medium intensity. Although 70% of peakVO_2_ is high- intensity, it is not ultra-high intensity. This study will explore the effects of these two different intensities.

AT intensity has not been widely accepted internationally. This study compares the effectiveness and safety of AT intensity and high intensity in patients with HF, and aims to reflect the superiority of AT intensity exercise. It has reference value for other colleagues in the world.

Limitations of the study should be recognized as follows: lost to follow-up, influencing factors including patient age, difficulties attending appointments, concurrent illnesses, and the nature of the intervention that made blinding impossible. We made every effort to ensure that evaluators, laboratory technicians and statisticians remain unaware of the treatment allocation.

Altogether, the results of the HF-EI trial may provide evidence on the effective delivery of a contextually adapted exercise-based CR program in China. At the same time, it provides evidence of AT exercise intensity for the world's CR field.

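### The safety stopping sentence halts the whole trial, is not tied to the data monitoring committee and leaves no option to stop one arm

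*Protocol article*

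**What the plan says.** All of the following is in the Protocol article.

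- **Trial Management and Quality Control, safety stop:** "Once serious side effects occur, the trial should be stopped immediately".
- **Same section, committee:** a data monitoring committee of three clinicians and two biostatisticians "independently evaluates the safety, scientific validity and completeness of clinical trials". It meets before recruitment and monthly once patients are being treated.
- **Same section, sentence just before the safety stop:** "The person in charge of the center monitors the intermediate results during the clinical trial".
- **Same section, sentence just after it:** if efficacy differs significantly between the three groups, "the trial will be considered to be terminated".
- **Intervention Group:** "Participants who have serious adverse clinical events during the intervention will immediately stop the intervention measures and withdraw from this clinical study".
- **Introduction:** "higher exercise intensity is associated with higher risk". The main comparisons are given as "Mainly compare MIT and HIT, or MIT and daily activities".
- **Discussion:** "This study compares the effectiveness and safety of AT intensity and high intensity in patients with HF".

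**The concern.** The sentence supplies a trigger, an action, a timing and an object, and the object is the trial. It does not link the decision to the committee charged with judging safety, and it does not allow for harm that is confined to one arm.

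That matters in this design. The high-intensity training (HIT) arm is the active control, and the authors expect risk to rise with intensity. A safety difference between HIT and moderate-intensity training (MIT) is part of what the trial sets out to learn. If exercise-related harm appeared only in HIT, the sentence taken literally would also stop MIT versus daily activities, whether or not MIT had shown any harm. The team would then have to choose between halting everything and departing from its own protocol.

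**Working it through.** **Is the stop at trial level?** The stopping rule carries no figure, so the first check is to set the texts side by side.

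1. The sentence following the safety stop uses the same noun for the study with all three groups. The natural reading of the safety sentence is therefore the whole study.
2. For efficacy, termination is only to be considered. For safety, no such discretion is written. The contrast makes the safety stop read as firmer.
3. The Intervention Group section already says what happens to an individual with a serious event. If the safety sentence meant only that individual, it would repeat the rule and name the wrong object. If it means the study, it goes well beyond that rule. Either way it needs rewording.
4. The committee has an independent safety remit, but no recommendation on stopping is assigned to it. The neighbouring sentence on watching interim results names the centre lead.
5. No sentence provides for stopping HIT while MIT and control continue.

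**How often might the sentence come into play?** The arm size comes from Statistical Methods: 60 per arm, 180 in total. It can be reproduced from the peak VO2 inputs. A three-group analysis of variance with mean variance (36 + 16 + 36)/3 = 29.3 needs 48 evaluable patients per arm (power 0.904), and 48/0.80 = 60. The stopping sentence does not affect this figure; it is used here only as an input. The two trained arms hold 2 × 60 = 120 patients.

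The article gives no rate of exercise-related serious events, so the per-patient risk p is **assumed**.

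- At least one event: 1 − (1 − p)^120
- At least two events: 1 − (1 − p)^120 − 120p(1 − p)^119

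| Assumed p | At least one in 120 | At least two in 120 |
|---|---|---|
| 0.1% | 1 − 0.999^120 = 0.113 | 0.007 |
| 0.5% | 1 − 0.995^120 = 0.452 | 0.122 |
| 1% | 1 − 0.99^120 = 0.701 | 0.338 |

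The second column of results is shown because the sentence uses a plural and does not say whether one case is enough.

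For a single arm of 60, 1 − (1 − p)^60 gives 0.058, 0.260 and 0.453 at the same three risks. These values apply equally to HIT and MIT, because the same p is used for both. They do not measure harm concentrated in HIT.

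**Limits of the calculation.** It covers all 120 trained patients over the whole intervention and does not model when an event occurs. A late trigger would cost little. Patients already past week 12 would have their primary outcome data, and the article does not say that event follow-up would end.

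**The case against.** The strongest reply has four parts.

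- **Thresholds and procedures belong elsewhere.** An article commonly leaves counts, boundaries and the committee's working rules to a full protocol or charter. This stands: the absence of a numerical boundary is not the point. What remains is a rule that the article does print, at trial level and without qualification. A fuller document that gave discretion would have to override it.
- **The stop need not be automatic, nor the committee excluded.** A reader might infer both. The documents do not support that. The sentence is passive and names no decision-maker, the committee evaluates safety independently every month, and the steering committee supervises the trial. Calling an event a side effect already needs a judgement on cause. The supportable statement is only that the stop is not tied to the committee.
- **The authors may have meant the individual participant.** This is plausible, since the wording resembles the Intervention Group rule and that rule presupposes that the trial goes on after a serious event. The object printed is nevertheless the trial, and the mismatch is itself a reason to amend.
- **A cautious stop is a legitimate choice in patients with an ejection fraction below 0.4.** This also stands. The clinical criterion belongs to the investigators and the committee, and the fix leaves it with them.

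A reader might also infer that the sentence contradicts the planned follow-up of deaths, heart failure admissions and major cardiovascular events. On the ordinary reading, in which side effects are harms caused by the exercise, it does not. A conflict would arise only if every serious clinical event counted.

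**Conclusion.** The point holds as a defect in a stated rule, and the sentence should be changed. It orders a trial-level stop without qualification, is not tied to the data monitoring committee and offers no arm-level option. It sits badly with the participant-level rule and with the aim of comparing safety between intensities. This conclusion rests on reading the sentence literally, which the neighbouring efficacy sentence supports.

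Its size cannot be established from the article. The range of about 11% to 70% for at least one event in 120 trained patients follows wholly from assumed risks of 0.1% to 1%. A reader might take it as the chance that the trial loses its comparisons. It is not: it is the chance that a qualifying event happens at some time if one event suffices, regardless of timing and of how the stop would be applied. No sample-size figure, error rate or analysis in the article is shown to be wrong.

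**What to change.** Replace the sentence with wording to this effect:

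- A serious intervention-related event stops training for that participant and triggers prompt review by the existing data monitoring committee.
- The committee may recommend pausing or stopping one arm or the whole trial, on the basis of between-arm data.
- The outcome events planned under Outcome Measures and Outcome Assessments do not by themselves end the trial.

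The clinical criterion for harm stays with the investigators and the committee.

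The cost is a wording amendment while the trial is recruiting, with steering committee and ethics approval. The committee and its monthly meetings already exist. Prompt review may need an extra meeting between the scheduled ones. Sample size, visits and outcome collection do not change, and the affected participant is still taken off training at once.
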